## Abstract

**OBJECTIVES::**

The Breathing Assistance in Children with bronchiolitis (BACHb) trial aims to evaluate the clinical and cost-effectiveness of high-flow nasal cannula (HFNC) therapy compared with humidified standard oxygen (HSO) in infants with moderate bronchiolitis, and HFNC with continuous positive airway pressure (CPAP) in severe bronchiolitis.

**DESIGN::**

Pragmatic, group-sequential, two-stratum, multicenter, open-label randomized clinical trial.

**SETTING::**

Fifty hospitals across England, Scotland, and Wales.

**PATIENTS::**

Hospitalized infants younger than 12 months old with a clinical diagnosis of bronchiolitis, assessed at least twice 15 minutes apart to fulfill criteria for either severe bronchiolitis (one or more of: respiratory rate > 70 breaths/min, grunting, marked chest recession, recurrent short apneas) or moderate bronchiolitis (lack of response to low-flow oxygen, indicated by persistent hypoxemia and/or moderate respiratory distress).

**INTERVENTIONS::**

“Moderate bronchiolitis stratum”: HFNC at a flow rate of 2 L/kg/min vs. HSO through a facemask or headbox at a flow rate up to 15 L/min. “Severe bronchiolitis stratum”: HFNC at a flow rate of 2 L/kg/min vs. CPAP pressure set at 6–8 cm H_2_O.

**MEASUREMENTS AND MAIN RESULTS::**

In each stratum, eligible infants will be randomly allocated on a 1:1 basis to the trial treatments using a web-based system by permuted block randomization, stratified by site of recruitment and age (< 6 wk and ≥ 6 wk). Due to the emergency nature of the treatments, written informed consent will be deferred. The primary outcome is time from randomization to hospital discharge within 30 days. Baseline clinical characteristics and hospital course, including details of respiratory support, and discharge and cost-effectiveness outcomes will be collected. The trial received Health Research Authority and Research Ethics Committee approval from the Yorkshire and The Humber—South Yorkshire Research Ethics Committee on August 3, 2023 (reference: 23/YH/0166). The trial registration is ISRCTN52937119.

**CONCLUSIONS::**

Trial findings will be disseminated in national and international conferences, in peer-reviewed journals and through social media.

RESEARCH IN CONTEXTBronchiolitis is a common reason for critical care admission, posing an enormous burden on hospitals worldwide, mainly during winter months, and is associated with considerable healthcare costs.Even though hypoxemia and breathing difficulties are the most important reasons for infants needing critical care admission, there are few well-powered randomized controlled trials comparing different modes of noninvasive respiratory support in infants with bronchiolitis-associated respiratory failure.The Breathing Assistance in Children with bronchiolitis (BACHb) trial is a group-sequential design, two-stratum, multicenter, open-label randomized clinical trial of respiratory support enrolling 1508 infants with acute bronchiolitis in 50 hospitals in the United Kingdom.

AT THE BEDSIDEThe BACHb trial is the first large multicenter adaptive randomized controlled trial in acute bronchiolitis to compare different modes of noninvasive respiratory support in infants with moderate as well as severe bronchiolitis.The two-stratum design allows results to be generated independently in each stratum (moderate and severe bronchiolitis) and allow early stopping of either stratum for efficacy without affecting the rest of the trial.The BACHb trial has the potential to produce important research findings, inform clinical practice as well as health policy worldwide, and lead to improvements in outcomes and the healthcare experience of infants with bronchiolitis and their families.

Bronchiolitis results in the hospitalization of approximately 30,000 infants per year in England (1, 2). Nearly 1000 require admission to a PICU, mainly for invasive ventilation (3, 4). This burden exacerbates existing staff and critical care bed shortages and accounts for considerable healthcare costs, partly from overuse of possibly ineffective treatments (5–9). A core aspect of bronchiolitis management is oxygen administration for hypoxemia and respiratory support for breathing difficulties (10). Guidelines commonly recommend low-flow oxygen (LFO) as the first step for oxygen supplementation in infants with hypoxemia (11). In sicker infants; however, there is ongoing uncertainty regarding the most effective methods of respiratory support (12).

Despite lack of evidence from well-powered randomized controlled trials (RCTs), high-flow nasal cannula (HFNC) therapy is widely used as an alternative to continuous positive airway pressure (CPAP) in infants with impending respiratory failure (13–16). HFNC is also commonly started in infants who “fail” treatment with LFO, based on physiologic and observational studies suggesting improved patient comfort and ease of use (17–19). In these infants, alternative options such as humidified standard oxygen (HSO) may provide adequate humidification and could be delivered in a ward environment with a lower nurse-to-patient ratio of 1:4 (compared with 1:2 for HFNC), with lower hospitalization costs (20–22). However, there are few RCTs comparing these methods of respiratory support.

The Breathing Assistance in Children with bronchiolitis (BACHb) trial is a group-sequential design, two-stratum, multicenter, open-label randomized clinical trial of respiratory support in infants with acute bronchiolitis. The trial will test the hypothesis that the first-line use of HFNC is superior to HSO in infants with bronchiolitis who have “failed” LFO (moderate bronchiolitis stratum) and CPAP in infants with impeding respiratory failure (severe bronchiolitis stratum) in reducing the time to hospital discharge.

## METHODS

The main aim of BACHb is to evaluate the clinical and cost-effectiveness of HFNC compared with HSO (in infants with moderate bronchiolitis) and CPAP (in infants with severe bronchiolitis).

### Primary Objective

The primary objective is to evaluate the effectiveness of HFNC compared with HSO (moderate bronchiolitis) and CPAP (severe bronchiolitis) in reducing the time to hospital discharge.

### Design and Setting

The trial is a pragmatic (23), four-stage group-sequential design, two-stratum, multicenter, open-label RCT with integrated health economic evaluation. The two-stratum design allows each stratum to produce independent results, as well as enabling early stopping for efficacy without affecting the rest of the trial.

A 6-month internal pilot phase (from October 2023 to March 2024) assessed key progression criteria of patient recruitment, and number of sites open to recruitment (green criteria: ≥ 40 sites open to recruitment, ≥ 150 patients enrolled and a recruitment rate of at least 1.1 per site per month). The trial funder recommended progression from the pilot stage to the full trial, based upon the recommendation of the Trial Steering Committee (TSC).

Study recruitment will continue to occur across Emergency Departments, inpatient pediatric wards and assessment units, and Paediatric Critical Care Units across England, Scotland, and Wales. Sites will be identified through the Paediatric Emergency Research in the United Kingdom and Ireland (PERUKI) (24), General and Adolescent Paediatric Research in the United Kingdom and Ireland (GAPRUKI) (25), and Paediatric Critical Care Society Study Group (PCCS-SG) (26). Sites are capable of administering the required trial treatments (HSO, HFNC, and CPAP), have collective equipoise between all possible treatments and comply with all study requirements as per the study protocol in addition to complying with legal and ethical requirements of the U.K. Policy Framework for Health and Social Care Research and the International Conference on Harmonization Guidelines on Good Clinical Practice (ICH-GCP).

### Study Population and Screening

The study population will include hospitalized infants with acute bronchiolitis (**Table 1**). Eligible patients will be screened by clinical and research staff, for the severe stratum first, and if inclusion criteria are not met, for the moderate stratum. Fulfillment of any exclusion criteria will result in the patient being ineligible. Ineligible patients will be recorded on site screening and enrollment logs, explaining reasons for exclusion.

**TABLE 1. T1:** Eligibility Criteria for the Breathing Assistance in Children With Bronchiolitis (BACHb) Trial

**Inclusion criteria (severe bronchiolitis**)
Hospitalized infants < 12 mo old with a clinical diagnosis of acute bronchiolitis, clinically assessed twice at least 15 min apart to have:
severe respiratory distress (one or more of: respiratory rate > 70 breaths/min, grunting, marked chest recession) and/or
recurrent short apneas (> 3/hr, each apnea lasting < 10 s)
**Inclusion criteria (moderate bronchiolitis**)
Hospitalized infants < 12 mo old with a clinical diagnosis of acute bronchiolitis, clinically assessed twice at least 15 min apart to have a lack of response to low-flow oxygen (up to 2 L/min), as indicated by:
persistent hypoxemia (oxygen saturation < 90%, or < 92% if age < 6 wk or if underlying health problems present) and/or
moderate respiratory distress (respiratory rate 55–70/min and/or moderate chest recession)
**Exclusion criteria**
1) Clinical decision that patient needs immediate intubation and ventilation for life-threatening hypoxemia, shock, or decreased conscious level
2) Prolonged apneas (> 10 s needing stimulation)
3) Ongoing active air leak (pneumothorax, pneumomediastinum)
4) Received humidified standard oxygen, high-flow nasal cannula, or continuous positive airway pressure for over 2 hr in the previous 24 hr
5) On home ventilation before hospital admission
6) Tracheostomy
7) Choanal atresia/stenosis, midfacial anomalies, or recent craniofacial surgery
8) Previously recruited to the Breathing Assistance in Children with bronchiolitis (BACHb) trial in the last 90 d

### Randomization and Concealment

Patients will be randomized as soon as possible following confirmation of eligibility to avoid delays in starting treatment. Randomization will occur at a 1:1 ratio using permuted blocks to either HFNC or HSO (moderate stratum) or HFNC or CPAP (severe stratum) using a web-based system (Sealed Envelope, London, United Kingdom), and stratified by the site of recruitment and infant’s age (< 6 and ≥ 6 wk). Once randomized into one stratum, patients cannot be randomized to the other stratum (e.g., from moderate to severe). The final randomization list was generated and stored by Sealed Envelope; none of the trial team members have access to the stored list, ensuring allocation concealment.

### Blinding

Since the medical devices and the interfaces that deliver the trial treatments are easily distinguishable from each other, it will not be possible to blind the subject or clinical staff.

### Study Treatments

#### Humidified Standard Oxygen

HSO will be delivered as per usual practice at each site using either a headbox or facemask attached to a heater/humidifier. The gas flow rate will be titrated between 6 and 15 L/min to maintain oxygen saturations greater than 90% (or > 92% for infants < 6 wk old or children of any age with underlying health conditions) (27).

#### High-Flow Nasal Cannula

HFNC will involve the delivery of heated, humidified gas through nasal cannula at the prescribed high-flow rate (2 L/kg/min). No specific device is recommended, and sites are expected to use their usual equipment.

#### Continuous Positive Airway Pressure

CPAP may be delivered using any medically approved device that can provide an expiratory pressure of 6–8 cm H_2_O that is used as part of the site’s usual practice.

### Clinical Practice During the Trial

In both strata, to minimize variations in practice, sites will follow study guidance for the commencement, continued delivery and weaning of treatment (**Figs. 1** and **2**). Infants will be assessed for tolerance, response and readiness to wean the assigned treatment at least every 6 hours. A BACHb trial nurse educator will support and train sites to deliver all trial-related treatments.

**Figure 1. F1:**
[figure not shown]
Algorithm for the initiation, weaning, switching, and escalation of treatment for the moderate stratum. BIPAP = bilevel positive pressure ventilation, CPAP = continuous positive airway pressure, FLACC = Face, Legs, Activity, Crying, and Consolability, HFNC = high-flow nasal cannula, HSO = humidified standard oxygen, Spo_2_ = oxygen saturation.

**Figure 2. F2:**
[figure not shown]
Algorithm for the initiation, weaning, switching, and escalation of treatment for the severe stratum. BIPAP = bilevel positive pressure ventilation, CPAP = continuous positive airway pressure, FLACC = Face, Legs, Activity, Crying, and Consolability, HFNC = high-flow nasal cannula, Spo_2_ = oxygen saturation.

If patients meet treatment failure criteria, they may be switched to the other arm within their allocated stratum or escalated to a higher form of respiratory support (including intubation) as “rescue treatment.” Patients escalated to bilevel positive pressure ventilation or invasive mechanical ventilation will be treated as per usual site practice (this will not be determined by the trial protocol). All other aspects of care including sedation and feeding for infants receiving the trial treatments will be decided by the treating clinical team.

### Consent Procedures

The BACHb trial will employ a “research without prior consent” (RWPC) model employed in previous trials conducted in pediatric emergency care settings (28–32). Consent will be deferred due to the need to commence urgent treatment and since attempts to obtain informed consent from families during a stressful emergency may compromise patient care. This approach was supported by families during two focus groups conducted as part of the BACHb trial design.

Written consent sought as soon as practically possible (usually within 24–48 hr) after randomization. Consent, using paper-based and electronic methods, will be sought for continued participation in the study, as well as the collection and recording of the child’s clinical data from medical records.

If parents are unable to be approached, or do not consent, before the child’s discharge, the local research team will contact parents by telephone to inform them of their child’s randomization to the study, and to provide study information by post or email (based on parental preference). If there is no response to the call, the local study delivery team will post a covering letter, a copy of the Parent Information Sheet and Informed Consent Form for parents to complete and return to the site. Four weeks after this initial postal contact, another contact attempt will be made stating that if there is no response, the child’s nonidentifiable data collected as part of routine care will be retained. In the rare event where an infant dies before consent has been obtained, a personalized letter will be posted to parents along with the bereaved versions of the consent form and information sheet. The letter will clarify that no further contact will be made, that parents’/legal guardians can refuse consent for their child’s data to be included, and that if there is no response, the child’s nonidentifiable data collected as part of routine care will be retained.

For infants whose parents do not provide informed consent, a minimal amount of data including the child’s month and year of birth will be retained as this will have been collected during the randomization process. However, clinical data after the point of randomization will be not be collected.

### Safety Monitoring

Safety and adverse event (AE) reporting will follow the guidelines of the Health Research Authority (HRA) on safety reporting in studies that do not involve Investigational Medicinal Products. The study protocol categorizes potential AEs of trial treatments which may occur between randomization and hospital discharge: 1) nasal trauma; 2) facial/neck trauma; 3) abdominal distension; 4) pneumothorax; 5) pneumomediastinum; 6) subcutaneous emphysema; 7) facial thermal injury; 8) respiratory arrest; 9) cardiac arrest; and 10) aspiration of gastric contents.

All AEs will be recorded and reported by sites through the OpenClinica system (OpenClinica, Needham, MA) and will be assessed for their severity and relatedness to the trial. Any AEs classified as “severe” or “life threatening” (i.e., “Serious AEs”) will be reported to the trial management teams within 24 hours. Serious AEs (SAEs) determined to be “related” and “unexpected” will be submitted by the Trial Management team to the Yorkshire and The Humber—South Yorkshire Research Ethics Committee (REC) within 15 days of the Chief Investigator being notified of the event.

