**Outcome measure**
1) Proportion of infants experiencing treatment failure
2) Mortality at hospital discharge, day 30, and day 90
3) Proportion of infants requiring intubation and ventilation
4) Proportion of infants requiring admission to an ICU
5) Proportion of infants requiring sedation
6) Duration of oxygen therapy, defined as the time to being free from supplemental oxygen for > 4 hr
7) Time to adequate (75%) oral feeding
8) Time ready for hospital discharge, defined as the time from randomization to latest of time to being free of supplemental oxygen or adequate oral feeding
9) Patient comfort, assessed by the caregiver using the Face, Legs, Activity, Crying, and Consolability scale
10) Patient comfort, assessed by the parent/guardian using a visual analog scale
11) Proportion of infants requiring hospital readmission within 30 d
12) Health status at 30 and 90 d
13) Cost-effectiveness expressed in terms of incremental cost per quality-adjusted life year gained

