### Statistical Methods

#### Sample Size

We assumed a median time to discharge of 5 days in the HSO group and 7 days in the CPAP group. The trial aims to detect a 20% reduction in HFNC compared with HSO in moderate bronchiolitis (hazard ratio [HR] = 1.25) and a 25% reduction compared with CPAP in severe bronchiolitis (HR = 1.33). To achieve 90% power at a 5% two-sided significance level, 860 events are required for the moderate group and 527 for the severe group.

Given the low competing risk of mortality (< 2%) and expected discharge within 30 days, we plan to recruit 462 infants per arm (moderate) and 292 per arm (severe), accounting for 7–9% censoring (death or hospital stay > 30 d) and consent refusals. Sample size calculations assume proportional hazards, four sequential tests with Lan-DeMets O’Brien-Fleming spending function. No multiple comparison adjustments are made, as the strata represent distinct treatment comparisons. Calculations were performed using rpact and validated with gsDesign3.3.0 (34, 35).

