#### Safety Analysis

AEs will be coded using Medical Dictionary for Regulatory Activities and summarized by severity, seriousness, and relatedness to treatment within each stratum. SAEs and Adverse Events of Special Interest will be reported in detail. The number of participants with at least one AE, the mean event count per participant, and occurence rates will be presented. If AE counts are sufficiently large, odds ratios and incidence rate ratios with 95% CIs will be estimated using appropriate regression models. Dot plots and horizontal stacked bar charts will visualize AE distributions and severity by treatment arm.

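### Safety Monitoring defines serious adverse events by severity grade, while Safety Analysis treats seriousness and severity as separate attributes; expedited reporting follows the severity-based rule

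*Protocol article*

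**What the plan says.** The Safety Monitoring section of the protocol article lists ten potential adverse events of the trial treatments, from nasal trauma to aspiration, that may arise between randomization and discharge. Sites record all adverse events in the trial database, where they "will be assessed for their severity and relatedness to the trial". The reporting rule comes next: "Any AEs classified as “severe” or “life threatening” (i.e., “Serious AEs”) will be reported to the trial management teams within 24 hours". The ethics-committee route is a subset of that group: "Serious AEs (SAEs) determined to be “related” and “unexpected” will be submitted by the Trial Management team", within 15 days of the Chief Investigator being notified. The section opens with a general reference: "Safety and adverse event (AE) reporting will follow the guidelines of the Health Research Authority (HRA") for studies without an investigational medicinal product.

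The Safety Analysis section says that adverse events will be coded and "summarized by severity, seriousness, and relatedness to treatment within each stratum", and that "SAEs and Adverse Events of Special Interest will be reported in detail".

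Deaths also appear outside the safety sections. Table 2 lists as a secondary outcome "Mortality at hospital discharge, day 30, and day 90".

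**The concern.** Severity describes how intense an event is. Seriousness describes what it leads to: death, a threat to life, a longer stay, lasting disability. A severe event may have no consequence, and an event of lesser intensity may have an important one. The two attributes are kept apart so that expedited reporting can follow consequence.

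The article joins them with an explicit equivalence. That is a stated rule, not a detail left out, and it decides which events reach the trial management team within 24 hours and which can go to the ethics committee. Infants enter this trial before consent is sought, and recruitment is ongoing, so the rule used for prompt safety reporting should be clear and should select the events that matter. It also decides what a planned summary by seriousness can show.

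**Working it through.** The trial states no figure on this point, so there is nothing to reproduce. The check sets the sections side by side and follows the rule to its consequences.

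**1. What is assessed.** Safety Monitoring names two attributes for each event, severity and relatedness. Seriousness is not among them.

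**2. How serious is defined.** The same section equates serious with two severity classes, severe and life threatening. The article gives no other criterion for seriousness and does not list the other grades of the scale.

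**3. What Safety Analysis needs.** It tabulates severity and seriousness as two attributes. If serious means severe or life threatening, then in every arm

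number serious = number severe + number life threatening.

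The seriousness table is then the sum of two rows of the severity table and adds no information. For Safety Analysis to be meaningful, seriousness has to be assessed in its own right, which the Safety Monitoring text does not provide for.

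**4. Where events go under the literal rule.**

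| Event | Serious by the stated rule | Serious by consequence | 24-hour report under the stated rule |
|---|---|---|---|
| Severe or life threatening, with serious consequence | yes | yes | yes, agrees |
| Severe, without serious consequence | yes | no | yes, over-reported |
| Graded below severe, lengthens the stay | no | yes | no, not expedited |
| Graded below severe, no consequence | no | no | no, agrees |

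The two middle rows are misrouted. A severe nasal abrasion that heals without consequence illustrates the second row, and a pneumothorax graded below severe that lengthens the stay illustrates the third. Both types of event are on the article's own list.

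**5. Fatal outcome.** It is not named as a trigger. Whether a fatal event is caught depends on the grade it receives. If the scale has a separate fatal grade, the literal wording leaves it out. If it has none, a fatal event would probably be graded life threatening and be caught. The article does not show which applies.

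**6. Ethics submission.** This is the related and unexpected subset of the serious set, so it inherits the same definition.

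**7. Size.** The number of misrouted events is the count in the two middle rows. The article gives no event rates by grade or by consequence, so that count cannot be derived.

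**The case against.** The strongest reply is that this is a condensed article of protocol version 3.0, which is not shown. The article says reporting follows Health Research Authority guidance and requires sites to comply with good clinical practice. The parenthesis may only abbreviate a fuller definition, and the list of seriousness criteria is the kind of detail an article leaves out. This stands as a limit on certainty: the fault is shown in the wording, not in what sites do. It does not remove the point. An explicit rule that conflicts with another section is more than an omission, and a general reference to guidance does not cancel a specific rule in the same section. If version 3.0 defines seriousness by outcome, the article misstates it; if not, the protocol needs the change.

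Other parts of the reply also stand. All adverse events are recorded whatever their grade. Prolonged stay and 30-day readmission are measured as outcomes, and so is mortality. These limit the harm, but an outcome count at the end of the trial is not an expedited report. For the ethics route, the listed events may well count as expected. If so, a listed event such as pneumothorax would not be submitted under either definition, and the effect there would be confined to unlisted events. Expediting a severe but inconsequential event is over-reporting and puts no infant at risk.

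Four stronger readings are tempting, and the article does not support them:

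- **Seriousness is not captured at all.** Safety Analysis plans a summary by seriousness, and the adverse event form is not shown. What is missing is a definition independent of severity.
- **About 30 deaths could go unreported.** The assumed mortality is below 2%, and 2 × 462 + 2 × 292 = 1508 infants, so 1508 × 0.02 = 30.2 is a ceiling on deaths. It does not count fatal adverse events that escape the 24-hour rule. To escape, such an event would have to be placed in neither named class.
- **The Data Monitoring Committee sees the wrong picture of harm.** The article says it reviews interim data for safety and efficacy and advises on safety events. Nothing restricts it to this set.
- **The comparison between arms is distorted.** The arms use different interfaces and staff are not blinded, so unequal misclassification is conceivable, but no figure supports it. The planned comparisons are framed on all adverse events, with serious ones reported in detail.

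**Conclusion.** The point holds as a conflict within the article with a practical consequence. Safety Monitoring defines serious by two severity grades and assesses only severity and relatedness; Safety Analysis requires seriousness as a separate attribute. Both cannot be carried out meaningfully as written. On a literal reading, the 24-hour report and the ethics submission are triggered by intensity, consequential events graded below severe are not expedited, and a fatal outcome has no stated place among the triggers.

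The defect is one of classification and expedited routing. Its size is unknown and cannot be worked out from the article. The conclusion assumes that the parenthesis is the operating definition; version 3.0, which could confirm or refute this, was not available. The reconciliation is worth making in either case, since the text as published states the rule wrongly.

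**What to change.** Reconcile Safety Monitoring with Safety Analysis:

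- Define a serious adverse event by outcome, whatever its severity grade: it results in death, is life-threatening, prolongs hospitalization or leads to rehospitalization, causes persistent or significant disability, or is otherwise medically important.
- Record seriousness as its own item, separate from severity, and add it to the attributes assessed for each event.
- Use that definition for the 24-hour report, for the ethics-committee submission of related and unexpected events, and for the table of serious events.
- Re-check the adverse events already entered against the new definition, and report any that should have been expedited.

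If version 3.0 and the adverse event form already work this way, correcting the article and confirming that sites follow the protocol is enough. Otherwise the cost is a change of protocol wording, one form field and a one-off re-check. No additional infants are needed.
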